## Assessment of seriousness

The SI will assess the seriousness of the event according to the criteria defined in section 14.1. Please note that according to section 14.2, death and a number of serious complications are suspected, and will therefore not be reported as SAEs/SADEs.

## Assessment of causality

This section is based on MEDDEV 2.7/3 revision 3 from the European Commission for the purpose of this trial.

1. **Not related:** relationship to the device or procedures can be excluded when:

- the event is not a known side effect of any intervention in this trial
- the event has no temporal relationship with the intervention in this trial
- the serious event does not follow a known response pattern intervention in this trial
- and is biologically implausible;
- the serious event can be attributed to another cause (e.g. an underlying or concurrent illness/ clinical condition, an effect of another device, drug, treatment or other risk factors);
- harms to the subject are not clearly due to use error;

In order to establish the non-relatedness, not all the criteria listed above might be met at the same time, depending on the type of device/procedures and the serious event.

1. **Unlikely:** the relationship with the intervention in this trial seems not relevant and/or the event can be reasonably explained by another cause, but additional information may be obtained.
2. **Possible:** the relationship with the use of the investigational device or intervention is weak but cannot be ruled out completely. Alternative causes are also possible (e.g. an underlying or concurrent illness/ clinical condition or/and an effect of another device, drug or treatment). Cases were relatedness cannot be assessed or no information has been obtained should also be classified as possible.
3. **Probable:** the relationship with the use of the investigational device seems relevant and/or the event cannot reasonably be explained by another cause, but additional information may be obtained.
4. **Causal relationship:** the event is associated with the intervention in this trial beyond reasonable doubt when:

- the event is a known side effect the intervention in this trial
- the event has a temporal relationship with the intervention in this trial
- the event involves a body-site or organ that the intervention in this trial are applied to or have an effect on;
- the serious event follows a known response pattern to intervention in this trial (if the response pattern is previously known);
- other possible causes (e.g. an underlying or concurrent illness/ clinical condition or/and an effect of another device, drug or treatment) have been adequately ruled out;
- harm to the subject is due to error in use;

In order to establish the relatedness, not all the criteria listed above might be met at the same time, depending on the type of device/procedures and the serious event.

## Assessment of severity

All AEs and SAEs will be assessed for severity, according to the Division of AIDS (DAIDS) Table for Grading the Severity of Adult and Paediatric Adverse Events, version 2.1 (July 2017).

The following guidelines will be used to describe severity.

Mild (Grade 1): Events that are usually transient and may require only minimal or no treatment or therapeutic intervention and generally do not interfere with the subject’s usual activities of daily living.

Moderate (Grade 2): Events that are usually alleviated with additional specific therapeutic intervention. The event interferes with usual activities of daily living, causing discomfort but poses no significant or permanent risk of harm to the research subject.

Severe (Grade 3): Events interrupt usual activities of daily living, or significantly affects clinical status, or may require intensive therapeutic intervention. Severe events are usually incapacitating.

Severe (Grade 4): Events that are potentially life threatening.

## Assessment of expectedness

The SI should assess expectedness for each SAE/SADE/USADE regardless of the causal relationship to the trial device.

Please note that death and a number of serious complications (including prolonged hospitalization and need of advanced medical and/or surgical interventions) are expected outcome after cardiac arrest and will not be reported as a SAE/SADE.

The expected adverse events of the REBOA catheters in use in this trial are mentioned in the instructions for use, appendix 29.3. Other catheter types may be available for use during the study period. These will be treated as recommended in the producers “instruction for use”. Eventual supplementary expected adverse event according to the producer of these catheter(s) will be registered as appropriate.

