## Exploratory endpoints

1. All-cause mortality one year after randomization
2. Difference in organ function, using the Acute Kidney Injury Network (AKIN) classification, liver function blood tests and others.
3. Incidence of all adverse events

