## Adverse events in the REBOARREST trial

Death is the most common outcome after cardiac arrest. Hence, we do not report death as a serious adverse event but register it as an expected outcome in the CRF.

All patients that achieve sustained ROSC will be transported to hospital and most will receive normal post-ROSC treatment, which include prolonged hospitalization and need of advanced medical and/or surgical interventions. It is therefore expected that nearly all subjects that achieve sustained ROSC will experience a serious adverse event after the definitions in this trial.

These SAEs are pre-specified outcomes and will not be reported but will be registered. We will therefore only report unexpected SAEs and SADEs/USADEs (events suspected related to the REBOA catheter and the handling of this equipment) to the sponsor and appropriate medicinal authority.

Adverse events will be documented in the CRF by the site investigator after the interview with the performing physician. If the patient is admitted to hospital, the SI will review the patient journal for documentation of adverse events 30 days after randomisation or if the patients dies prior to this. Adverse events that occur after this time will not be reported.

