## Period for recording adverse events

For each patient the standard period for collecting and recording AE will be from randomization and until admission to hospital.

For each patient the standard period for collecting and recording SAE will be from allocation and until the 30 day follow up visit. At the 30 day visit an assessment will be made where we specifically ask for all SAEs prespecified in this protocol. We will also assess discharge notes for other events that fulfil the SAE definition and that can be assessed by the study team.

For patients still admitted to hospitals at day 30, an effort will be made to secure access to main discharge note for assessment for any SAE that has occurred between day 30 and discharge.

Any information that comes to investigators attention for any included patient prior to the end of trial will be assessed according to this protocol.

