### Reporting to appropriate medicinal authorities

Serious adverse device effects (SADE) and unanticipated serious adverse device effects (USADE) shall be reported to the Norwegian Medicines Agency by the responsible site. The incident report “Meldeskjema for virksomhet som bruker medisinsk utstyr” is found at the Norwegian Medicines Agency website (<https://legemiddelverket.no/medisinsk-utstyr/meld-korrigerende-tiltak-feil-og-uonsket-hendelse-med-medisinsk-utstyr>). SADE or USADE causing death or life-threatening illness or injury should be reported not later than 2 calendar days following the date of sponsor awareness, other SADE/USADE should be reported not later than 7 calendar days.

SADE and USADE should also be reported to the Norwegian Board of Health Supervision. As described on the boards webpage [www.helsetilsynet.no](http://www.helsetilsynet.no), this report should be emailed to [[contact]](mailto:[contact]).

This report should contain:

- The site investigators name and title
- Telephone number to the site investigator and information on when best to be contacted
- What special field in which the research is performed (emergency medicine) and which study site.

No health or identifiable information should be included in this report. The report should be sent as soon as possible after the SADE/USADE is discovered.

It is the responsibility of the chief investigator to ensure that each site investigator report such events from their site.

The current protocol describes the reporting procedures to Norwegian Authorities. Foreign study sites will have this section updated according to national procedures.

Each site must ensure compliance with the local hospital’s procedures relating the use of medical equipment.

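### Sections 14.3 and 14.6 exempt anticipated device-related deaths from the SADE reporting that 14.2 and 14.9.2 require, and the adverse-event window is given two different ends

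*Protocol*

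**What the plan says.** **Reporting.** Section 14.6 opens with a rule that applies whatever the cause: "The SI should assess expectedness for each SAE/SADE/USADE regardless of the causal relationship to the trial device". It then says that death and a number of serious complications, including prolonged hospital stay and the need for advanced medical or surgical treatment, "are expected outcome after cardiac arrest and will not be reported as a SAE/SADE". Section 14.3, pointing back to 14.2, says that "death and a number of serious complications are suspected, and will therefore not be reported as SAEs/SADEs". It does not mention surgery.

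Section 14.2 is narrower on death: "we do not report death as a serious adverse event but register it as an expected outcome in the CRF". That sentence concerns SAEs and does not mention SADEs. The same section goes on to say that unexpected SAEs, SADEs and USADEs (unanticipated SADEs) are what is reported to the sponsor and the authority. It describes the device categories as events suspected to be related to the catheter and its handling.

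Section 14.9.2 sends SADEs and USADEs to the Norwegian Medicines Agency. It adds that "SADE or USADE causing death or life-threatening illness or injury should be reported not later than 2 calendar days" after the sponsor becomes aware, and allows 7 days for the others. Section 14.8 says that expected serious events are recorded in the CRF but not passed to the sponsor.

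**Collection window.** Section 14.7 says that the standard period for "collecting and recording AE will be from randomization and until admission to hospital", while SAEs run to the day-30 visit. Section 6.5 lists "Incidence of all adverse events" as an exploratory endpoint.

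**The concern.** SADE is by definition the device-related class (14.1). An exemption that names SADE therefore covers harm caused by the catheter, and nothing in 14.3 or 14.6 takes it out again. Other sections require the same event to be reported on a short clock. A site cannot follow both.

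The intervention is invasive and given under deferred consent, and most patients are expected to die of the arrest. A device-caused death is then easily filed as the expected outcome, so the rule for separating the two must be unambiguous.

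The second conflict bears on the comparison of harms. If one site stops recording non-serious events at admission and another continues to day 30, the incidence of all adverse events has no fixed meaning. The dated complication fields in 12.2 concern REBOA equipment only, so in the control arm the post-admission count depends wholly on which section the site follows.

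**Working it through.** No sample size, error rate or event count enters this point. The check is to take concrete events through the sections.

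**1. Fatal rupture of a vessel by the catheter.**
- 14.1: related to the device and led to death, so a SADE.
- 14.6, list of REBOA-related events: vessel rupture is expected, and 13.1.3 discusses aortic rupture as a risk. It is therefore probably an anticipated SADE and not a USADE.
- 14.3 and 14.6: not reported as a SADE.
- 14.2 and 14.9.2: reported, within 2 calendar days of sponsor awareness.
- Result: contradiction. If the site also reads 14.8 as covering the event because it is expected, the sponsor is not told. The clock, which runs from sponsor awareness, then may never start.

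**2. Catheter-related access injury that needs surgery, patient survives.**
- 14.6: not reported as a SADE, because need of surgery is in the exempt class. 14.3 does not name surgery.
- 14.2 and 14.9.2: reported, within 7 calendar days, or 2 if life-threatening.
- Result: the same contradiction, resting on 14.6.

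**3. Death from a device effect not identified in the risk analysis.**
- 14.1: a USADE.
- 14.3 and 14.6 name SAE and SADE, not USADE. 14.2 and 14.9.2 require a report.
- Result: no exemption is stated for this class.

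**4. Death from the arrest, with no suspicion of the device.**
- 14.2, 14.3 and 14.6 agree: registered, not reported. 14.9.2 does not apply.
- Result: no conflict. The problem is confined to anticipated SADEs.

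**5. Non-serious puncture-site haematoma on day 3 in hospital.**
- 14.7: after admission and not serious, so outside the window.
- 14.2: inside, because the site investigator reviews the hospital record for adverse events at 30 days.
- 14.8: inside, because events up to day 30 are collected from the discharge note and paper CRF, without restriction to serious ones.
- 10.3: adverse reactions over 30 days are to be reported.
- 12.2: has a dated CRF field only if there is local bleeding that needs treatment.
- Result: whether it counts towards the endpoint in 6.5 depends on the section read.

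**The case against.** The best defence is that the intent is clear. Section 14.3 rests on 14.2, and 14.2 says that SADEs are reported. Section 14.6 speaks of outcomes following cardiac arrest, which can be read as meaning the natural course. Under 14.9.1 anyone who suspects a SADE reports it within 72 hours, and the chief investigator makes the final assessment. The reportable-events flowchart, which is not shown in the text available here, may also settle the route. This stands as evidence of intent: device-related deaths were probably meant to be reported. It does not cure 14.3 and 14.6, which name SADE in the exemption. Even a clear flowchart would leave two sections contradicting it.

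Several stronger readings are tempting but unsupported:

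- **That these harms would be missed.** Not reporting is not the same as not recording. Deaths and expected SAEs go into the CRF (14.2, 14.8), and SAEs are actively sought at day 30 (14.7). Each randomised patient's case has a physician interview and external expert review (13.1.1), and a data monitoring committee is planned (section 22). What is at risk is timely reporting.
- **That every device-caused death is exempt.** USADEs are not.
- **That the size follows from overall mortality.** At the quoted 14% national survival, 200 × (1 − 0.14) = 172 deaths. That figure covers all Norwegian out-of-hospital arrests, not the eligible cohort, and says nothing about deaths caused by the device.
- **That the pilot shows a device harm that would now be hidden.** One of 10 pilot patients had an ischaemic colon with hemicolectomy. It was reported, and the investigation concluded that REBOA was not the cause (13.1.3). It shows only that causality can be settled after reporting.
- **That adverse-event collection stops at admission.** Only 14.7 says so. The documents show an inconsistent window, not a settled stop.

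**Conclusion.** Two internal contradictions stand and should be corrected.

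First, 14.3 and 14.6 exempt death and a number of serious complications from SADE reporting with no exception for device-related cases, against 14.2 and 14.9.2. An anticipated fatal device effect is both exempt and reportable. A rule followed as written would give the wrong safety result, and correcting it is cheap. This rests on reading SADE as 14.1 defines it and on vessel rupture being listed as expected in 14.6.

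Second, 14.7 ends adverse-event recording at admission, against 14.2, 14.8, 10.3 and the in-hospital fields of 12.2. The window for the all-adverse-events endpoint is therefore not fixed.

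Neither has a numerical size that the documents can support. The first affects only anticipated SADEs, whose frequency is not given. The second affects an exploratory endpoint and leaves the primary analysis of ROSC untouched.

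**What to change.** Reconcile 14.2, 14.3, 14.6, 14.8 and 14.9.2. Delete SADE from the exemptions in 14.3 and 14.6, and state there and in 14.8 that the exemption does not cover events suspected to be related to the REBOA catheter or its handling, which is the test 14.2 already uses. Check that the flowchart in 14.8 agrees.

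Align 14.7 with 14.2, 14.8 and 10.3: record adverse events to day 30 in both arms, using the chart review already planned in 11.2. State this window with the endpoint in 6.5.

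The cost is a text amendment, a site notice and some additional reports; no visit is added. The number of reports depends on how many deaths are suspected to be device-related. Section 14.4 grades relatedness that cannot be assessed as possible, and autopsy consent is sought only for patients admitted in Norway who die before discharge (13.1.4), so the amendment should say whether that grade counts as suspected. If the 14% national survival applied to the 100 REBOA patients, 100 × (1 − 0.14) = 86 would die. Under that assumption, additional death reports could lie anywhere from 0 to 86, and the documents do not narrow the range.

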**Expected adverse events common to both treatments**

- Death
- Multi-organ failure
- Extremity ischemia
- Abdominal and/or pelvic ischemia that may/may not require surgical intervention
- Stroke (embolic or related to hypoperfusion)
- Paralysis
- Paraplegia, permanent or temporary
- Renal complications requiring renal replacement therapy

**Expected adverse events related to use of REBOA**

Adverse events related to access

- Vessel dissection, perforation, rupture or injury
- Paraesthesia
- Infection, hematoma and/or pain at insertion site, with/without need for surgical intervention
- Haemorrhage at insertion site requiring treatment
- Pseudo-aneurysm
- Arteriovenous fistula
- Air embolism
- Arterial thrombosis, dissection, stenosis and/or embolism
- Need for arterial bypass
- Need for amputation

Other adverse events

- Contrast reactions
- Balloon rupture
- Occlusion at some locations may cause arrhythmia
- Aneurysm rupture

**Expected adverse events related to standard ACLS**

- Cardiac events and/or injury
- Thoracic aortic injury
- Lung injury/bronchopleural injury
- Oesophageal injury
- Respiratory failure
- Rib fractures
- Sternal fractures
- Aspiration pneumonia requiring antibiotic
- Injury to the gastric ventricle or liver

## Period for recording adverse events

For each patient the standard period for collecting and recording AE will be from randomization and until admission to hospital.

For each patient the standard period for collecting and recording SAE will be from allocation and until the 30 day follow up visit. At the 30 day visit an assessment will be made where we specifically ask for all SAEs prespecified in this protocol. We will also assess discharge notes for other events that fulfil the SAE definition and that can be assessed by the study team.

For patients still admitted to hospitals at day 30, an effort will be made to secure access to main discharge note for assessment for any SAE that has occurred between day 30 and discharge.

Any information that comes to investigators attention for any included patient prior to the end of trial will be assessed according to this protocol.

## Recording of adverse events

Patients in this trial are critically ill and are expected to need a prolonged hospital stay, often in intensive care unit and with several interventions. Both the standard care prior to arrival in hospital and during their stay have significant risks for adverse events. Expected serious adverse events will be recorded in the CRF, but not reported to the sponsor.

Adverse events occurring between allocation and the end of treatment phase by pre-hospital services will be fully recorded. Events occurring between end of treatment by pre-hospital services and day 30 will only be collected by checking hospital discharge note and paper CRF filled in by the SI after contact with the admitted hospital. The SI will assess the event for seriousness, causality, severity and expectedness before the event is registered in the CRF.

**Adverse event/device effect: Reportable events flowchart**

[figure not shown]

## Reporting of SAE/SADE/USADE

### Reporting from study site to chief investigator

A separate SAE/SADE/USADE form will be part of the CRF. Anyone suspecting a SAE/SADE/USADE should report this to the SI and/or the chief investigator as soon as possible and within 72 hours (3 days). The chief investigator makes the final assessment regarding seriousness, causality, severity and expectedness and need for further reporting.

A report of a suspected SAE/SADE/USADE must minimum include the unique study number of the participant, description of AE, initial assessment of AE for seriousness, causality, severity and expectedness and the identity of the person reporting.

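### Whether a serious aortic injury, limb or abdominal/pelvic ischaemia or paraplegia in a REBOA patient is reported during the trial depends on a causality call that the chief investigator may set below the site's suspicion

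*Protocol*

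**What the plan says.** Section 14.6 gives three lists of expected events. The one headed "Expected adverse events common to both treatments" includes "Extremity ischemia", "Abdominal and/or pelvic ischemia that may/may not require surgical intervention" and paraplegia. The list for standard ACLS includes "Thoracic aortic injury". The list for REBOA includes "Vessel dissection, perforation, rupture or injury".

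Section 14.8 states the consequence of being expected: "Expected serious adverse events will be recorded in the CRF, but not reported to the sponsor". Section 14.2 says the same from the other side. Only unexpected serious events, and serious device effects where a link with the catheter or its handling is suspected, go to the sponsor and the authority.

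Section 14.8 has the site investigator assess seriousness, causality, severity and expectedness first. Section 14.9.1 then provides: "The chief investigator makes the final assessment regarding seriousness, causality, severity and expectedness and need for further reporting". It also requires each report to carry the initial assessment and to identify who made it. Under section 14.9.2, serious device effects, anticipated or not, "shall be reported to the Norwegian Medicines Agency by the responsible site".

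**The concern.** The balloon is inflated in zone 1 of the aorta and limits flow to everything below it. Section 13.1.3 names aortic damage, limb ischaemia and organ ischaemia as risks of the procedure. The same kinds of injury are on the expected lists for ACLS or for both treatments, so being serious is not enough to have them reported. What decides is the view on causality, and one person, who leads the trial, has the last word on it.

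The trial's own pilot shows why the order of steps matters. Section 13.1.3 describes one pilot patient (of 10, section 9.2) with ischaemic colon and a hemicolectomy. That event was reported to the authorities first, and the investigation that followed concluded that REBOA was not the cause. Under the present text an event of that kind is on the common list. If the chief investigator judged it unrelated at the outset, sections 14.2 and 14.8 would not call for a report. At stake is what the sponsor and the authority see while an invasive procedure is being tested under deferred consent.

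**Working it through.** There is no figure to reproduce. The check follows one event through the sections: a serious aortic injury, limb ischaemia, abdominal/pelvic ischaemia or paraplegia in a REBOA patient.

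1. *Expectedness (14.6).* REBOA patients also receive ACLS, so both the ACLS list and the common list apply to them. The event is expected.
2. *Unexpected-event route (14.2, 14.8).* Closed, because the event is expected.
3. *Device route (14.1, 14.2, 14.9.2).* Section 14.1 makes an adverse event a device effect when it is related to use of the device, and a serious device effect when it also has the consequences of a serious event. Section 14.9.2 then requires a report whether or not the effect was anticipated. This is the only route left, and it depends on causality.
4. *Who decides (14.8, 14.9.1).* The site assesses first and the chief investigator last. No sentence limits the direction of a change.

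The possible combinations, if the final view governs:

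| Site's view | Chief investigator's view | Resulting class | Sent to sponsor or authority during the trial |
|---|---|---|---|
| suspected | related | serious device effect | yes (14.2, 14.9.2) |
| not suspected | related | serious device effect | yes |
| suspected | not related | expected serious event | no (14.8) |
| not suspected | not related | expected serious event | no |

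The third row is the gap. The suspicion named as the threshold in section 14.2 existed at the site, and the event is still not sent.

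5. *Control arm.* No catheter is used, so the device route cannot apply. The same event in a control patient is an expected serious event and has no route to the sponsor during the trial. Case reports alone would therefore not let the sponsor compare the arms on these injuries.

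6. *Two loose ends on the same path.* Section 14.4 defines five causality grades, but no visible text says which of them make an event a serious device effect. Separately, sections 14.3 and 14.6 say that some serious complications will not be reported even as serious device effects, and 14.6 includes the need for surgical intervention among them. Sections 14.2 and 14.9.2 require serious device effects to be reported. These sections must be reconciled.

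**The case against.** Much can be said for the present text, and most of it stands as a limit on the point.

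- *The site's view is not lost.* A reader might infer that a disagreement leaves no trace. Section 14.9.1 requires the initial assessment and the reporter's identity, and section 14.8 has the site assess all four attributes before CRF entry. What is missing is a rule on which view governs reporting.
- *Sections 14.9.1 and 14.9.2 need not conflict.* A reader might take them as opposite instructions. They can be read in sequence: 14.9.1 classifies, and 14.9.2 acts on what has been classed as a serious device effect. That reading removes the contradiction, but it is also the reading under which the chief investigator's classification decides the outcome.
- *The causality rules lean towards relatedness.* Under section 14.4 a weak link that cannot be excluded is graded possible, and so is a case that cannot be assessed. The REBOA list names vessel injury, which makes it a known effect. This narrows the gap but does not close it. The same section allows a lower grade when another cause is a reasonable explanation, and in cardiac arrest such a cause is often at hand.
- *Other eyes on the data.* An external panel reviews every randomised patient (13.1.1), prespecified serious events are asked for at day 30 (14.7), the clinical research unit collaborates on adverse events and monitoring (section 20), and a DMC is planned (section 22). The protocol gives the panel no stated part in this classification. The DMC charter is a separate document, so one cannot say that the DMC has no role.
- *No stopping rule is affected.* A reader might assume that the number of serious device effects drives a safety stop or is the main safety result. Neither section 11.3 nor section 6.5 says so. The listed endpoint is the incidence of all adverse events.
- *Lack of blinding adds little.* Nobody can judge whether a balloon caused an injury without knowing that a balloon was used.

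The reportable-events flowchart is not shown here and may settle which causality grades trigger a report.

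**Conclusion.** The point holds in a limited form. For serious aortic injury, limb ischaemia, abdominal/pelvic ischaemia and paraplegia in REBOA patients, reporting to the sponsor or authority during the trial rests on causality alone, and section 14.9.1 allows a site's suspicion to be lowered with no stated limit.

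It would be too strong to say that these events could vanish from the results. They remain in the CRF, and a between-arm comparison of the incidence of all adverse events (6.5) needs no attribution. No analysis of efficacy is touched.

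No numerical size can be given. The protocol states no expected rate for these events and no rate of disagreement between site and chief investigator. The conclusion rests on two assumptions: that the final assessment prevails over the initial one, and that neither the flowchart nor the DMC charter already contains a rule for disagreement or a separate route for these events. It is a worthwhile and cheap change to a stated reporting rule, and it does not show that any event would in fact be misclassified.

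**What to change.** In section 14.9.1, add that the chief investigator may raise but not lower the site's assessment of seriousness or causality, and that reporting and tabulation follow the more serious or more related of the two assessments. Both assessments are already to be documented, so this only fixes which one governs.

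In section 14.8, add that serious aortic injury, limb ischaemia, abdominal/pelvic ischaemia and paraplegia are sent to the sponsor and the DMC from both arms, regardless of expectedness and causality. The DMC charter should name the same list.

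In the same edit, state which causality grades count as a suspected link (or refer to the flowchart if it says so), and reconcile sections 14.3 and 14.6 with 14.2 and 14.9.2 on whether any serious device effect is exempt from reporting.

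The cost is a few sentences and a few more serious-event reports from both arms. Treatment, endpoints, sample size and analysis are unchanged.
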